##### Adherence monitoring

Patients will return empty packets at each visit. Adherence will be calculated as (packets consumed / packets dispensed) × 100%, with ≥80% defined as adherent. Dose intensity, treatment interruptions, and modification rules will be recorded.

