#### Follow-up and assessments

Follow-up visits will occur every 3 months, as outlined in Table 2, and will include clinical evaluation, imaging studies, laboratory testing, and assessment of adverse events. Imaging for tumor response assessment will be performed every 8 weeks from randomization until disease progression. The efficacy of YFXJD will be evaluated through progression-free survival, TCM symptom scores, activity levels, biochemical parameters, and exploratory biological indicators. Safety will be assessed according to protocol-defined criteria. The trial flowchart is presented in Figure 1.

**Table 2 tab2:** Schedule of trial.

Assessment/Time point	Screening	Baseline/Initiation	Treatment period	Treatment period	Long-term follow-up	End-of-treatment visit	Survival follow-up
	D -7	D0	D90 ± 7	D180 ± 7	D365 ± 7	Upon PD/Discontinuation	
Procedures							
Informed consent	✓						
Eligibility review	✓						
Data collection							
Demographic information	✓						
History of NSCLC & treatment	✓						
History of other diseases	✓						
Randomization & drug dispensing		✓	✓ (Re-supply)	✓ (Re-supply)			
Primary endpoints							
1. PFS (RECIST 1.1)			Imaging per protocol	Imaging per protocol	Imaging per protocol	✓ (Confirm PD)	Record death
2. TCM Syndrome Score	✓ (Baseline)		✓ (Interim)	✓ (Primary Time Point)			
Secondary endpoints (Efficacy)							
Tumor response (ORR/DCR)			✓	✓	✓	✓ (Final)	
Quality of life (EORTC QLQ)	✓ (Baseline)		✓	✓	✓		
Performance status (KPS)	✓ (Baseline)		✓	✓	✓		
Biomarkers							
Lymphocyte subsets	✓ (Baseline)		✓	✓	✓		
Inflammatory cytokines	✓ (Baseline)		✓	✓	✓		
Tumor markers	✓ (Baseline)		✓	✓	✓		
Safety assessments							
Clinical laboratory tests							
CBC, hepatic & renal function	✓	✓	✓	✓	✓	✓	
Urinalysis & stool routine	✓	✓	✓	✓	✓	✓	
AE/SAE collection	✓	✓	✓	✓	✓	✓	
EGFR-TKIs specific AE recording		✓	✓	✓	✓	✓	
Concomitant medication record		✓	✓	✓	✓		
Proportion with dose Mod./Disc.			Recorded	Recorded	Recorded	✓ (Final)	
Study administration							
Protocol deviation record		✓	✓	✓	✓		
CRF completion		✓	✓	✓	✓	✓	

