#### TCM intervention

The TCM intervention will be administered concurrently with EGFR-TKIs therapy and will continue until disease progression, unacceptable toxicity, or other criteria for treatment discontinuation are met. Both the YFXJD and placebo are manufactured as granules. Each sealed packet contains a fixed dose of granules (10 g per packet, 5:1 extraction ratio), with identical packaging to ensure complete blinding in terms of appearance, texture, smell, and taste. Matching placebo granules with similar appearance, odor, taste, and packaging, without active herbal ingredients. Are composed of pharmaceutical-grade excipients (primarily maltodextrin) with approved food colorants and flavorings.

Quality control of YFXJD granules includes: (1) botanical authentication of all raw herbs with voucher specimens deposited at the Shanghai University of TCM Herbarium; (2) compliance with Chinese Pharmacopoeia 2020 edition standards; (3) chemical fingerprinting by HPLC for batch-to-batch consistency; (4) 12-month stability testing; and (5) testing for pesticides, heavy metals, microbes, and adulterants. The YFXJD granules and placebo are produced under Good Manufacturing Practice (GMP) standards at Sichuan Neo-green Pharmaceutical Technology Development Co., Ltd. The manufacturer supplied the study products but had no role in study design, data collection, analysis, or manuscript preparation; no financial or non-financial competing interest exists.

Patients will be instructed to dissolve the contents of one packet in approximately 150–200 mL of hot water and to take it orally twice daily (morning and evening), 30 min after meals. The daily total dose will therefore consist of two packets. The dosage and administration frequency will remain constant throughout the treatment period unless modified due to tolerability issues as assessed by the investigator.

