### Outcomes

#### Primary outcomes

Progression-Free Survival (PFS): Defined as the time from randomization to the first occurrence of radiographic disease progression according to RECIST 1.1 (15) criteria or death from any cause, whichever occurs first. Imaging will be performed every 8 weeks from randomization until disease progression, with blinded independent central review.

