### Statistical analysis

The statistical analysis will be performed using SAS statistical software (version 9.4). The primary analyses for efficacy and safety will be conducted according to the Intention-to-Treat (ITT) principle, including all randomized participants in the groups to which they were assigned. A per-protocol (PP) analysis will also be performed as a supplementary analysis.

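### Adherence is divided by packets dispensed rather than packets due, so a patient with perfect intake who stops early in a supply may be labelled non-adherent

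*Protocol article*

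**What the plan says.** Under Adherence monitoring, the protocol article fixes both formula and cut-off: "Adherence will be calculated as (packets consumed / packets dispensed) × 100%, with ≥80% defined as adherent". The count of packets taken comes from returns: "Patients will return empty packets at each visit". Nothing there subtracts unused packets or limits the denominator to days on treatment.

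Three other places determine how the formula behaves:

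- **Dose and duration (TCM intervention).** "The daily total dose will therefore consist of two packets". The granules "will continue until disease progression, unacceptable toxicity, or other criteria for treatment discontinuation are met".
- **Supply (Table 2).** The row "Randomization & drug dispensing" is ticked at D0, with re-supply at D90 and D180. No packet count is given, and no re-supply is ticked after D180. The accompanying text says: "Follow-up visits will occur every 3 months, as outlined in Table 2".
- **Detection of progression (Primary outcomes).** "Imaging will be performed every 8 weeks from randomization until disease progression".

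The Statistical analysis section makes ITT the primary approach and adds: "A per-protocol (PP) analysis will also be performed as a supplementary analysis". It does not say how the per-protocol set is formed.

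**The concern.** An adherence ratio should compare what a patient took with what the patient was meant to take. Here the denominator is what was handed over. The two agree for a patient who finishes a supply. They part when treatment ends within a supply, because the remaining packets were dispensed but never due.

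The scans fall on days 56, 112, 168, 224 and so on, out of step with re-supply at days 90 and 180, so progression found on a scan will usually stop treatment part-way through a supply. The label then depends on when the patient stopped as well as on what the patient took. Since progression is the main planned reason for stopping, the label becomes partly a function of the primary endpoint. Stops for toxicity or withdrawn consent produce the same artefact.

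At stake are the reported adherence rate, the adherent/non-adherent label, and any analysis that might later use that label.

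**Working it through.** The document gives no adherence forecast to reproduce, so the check applies its formula to a patient with perfect intake.

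**Inputs.** 2 packets per day (TCM intervention). Dispensing at D0, D90 and D180 (Table 2). Scans every 8 weeks (Primary outcomes). Median PFS 18.9 and 28.6 months (Sample size).

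**Assumptions.** The first two supplies last 90 days, i.e. 180 packets each. The third supply's length is not stated, so it is run to D270 (180 packets) and to D365 (2 × 185 = 370 packets). Intake is perfect, progression is the only reason for stopping, and PFS is exponential.

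**Step 1: score at each scan.** Adherence = 2 × stop day / cumulative packets dispensed.

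| Stop at scan | Third supply to D270 | Third supply to D365 |
|---|---|---|
| Week 8 (day 56) | 112/180 = 62.2% | same |
| Week 16 (day 112) | 224/360 = 62.2% | same |
| Week 24 (day 168) | 336/360 = 93.3% | same |
| Week 32 (day 224) | 448/540 = 83.0% | 448/730 = 61.4% |
| Week 40 (day 280) | beyond this supply | 560/730 = 76.7% |
| Week 48 (day 336) | beyond this supply | 672/730 = 92.1% |

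The same perfect intake passes or fails according to the stop date.

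**Step 2: stop days that fail 80%.** The score reaches 80% at 0.8 × the last day covered by supply so far: day 0.8 × 90 = 72, day 0.8 × 180 = 144, and day 0.8 × 270 = 216 or 0.8 × 365 = 292. Failing windows are days 0-72, 90-144, and 180-216 or 180-292.

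**Step 3: share of patients in those windows.** S(t) = exp(−ln 2 × t / (30.4375 × median)), with t in days and the median in months.

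*Stopping on the day of progression:*
- Control, to D270: 0.083 + 0.057 + 0.034 = 17.4%. To D365: 0.083 + 0.057 + 0.102 = 24.1% (terms rounded).
- YFXJD, to D270: 0.056 + 0.039 + 0.024 = 11.9%. To D365: 0.056 + 0.039 + 0.074 = 16.9% (terms rounded).

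*Stopping at the scan that finds progression:*
- To D270, only the week-8 and week-16 scans fail: 1 − S(112) = 12.6% control, 8.5% YFXJD.
- To D365, weeks 32 and 40 also fail: add S(168) − S(280), giving 12.6 + 10.3 = 22.9% control and 8.5 + 7.5 = 16.0% YFXJD.

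The range is therefore about 13-24% of control and 9-17% of YFXJD patients. It counts only stops within the three supplies in Table 2.

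**Step 4: per-supply reading.** The document does not say whether the ratio is cumulative or per supply. Taken on the current supply alone, the week-8, week-16 and week-24 scores are 62.2%, (112 − 90)/90 = 24.4% and (168 − 90)/90 = 86.7%. The artefact appears either way.

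**Step 5: with packets due as denominator.** The same patient scores 112/112 at week 8, 224/224 at week 16, and 100% at every other stop date.

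**The case against.** The strongest reply is that nothing in the document uses the label. The primary analysis takes all randomized patients, the safety population needs only one dose, and no text ties the 80% rule to the per-protocol set. This stands. A reader might infer that the per-protocol analysis would selectively lose early progressors, because this is the only adherence threshold given and such an analysis is planned. The document does not make that link, so the consequence is conditional.

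Second, not every mid-supply progression is mislabelled. Stops late in a supply pass: week 24 scores 93%, and week 48 scores 92% with a supply to D365. This stands, and it limits the point to stops early in a supply.

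Third, the upper figures need a third supply of 185 days. Table 2 shows no re-supply after D180 although treatment runs to progression, so it may not be a complete dispensing record, and visits are described as three-monthly. This also stands and is why a range is given.

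Fourth, the gap between arms is not built into the formula. It comes from the assumed medians. With no treatment effect, progression would mislabel both arms equally.

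It may also be said that dose intensity and interruptions are recorded, and that the counting of leftovers belongs in the full protocol or SAP. This helps little. The article does not leave the denominator open; it fixes it as packets dispensed, and a SAP that used packets due would contradict it.

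**Conclusion.** The concern holds in limited form. The stated formula gives a wrong adherence value for patients who stop early in a supply, and it can label a patient with perfect intake non-adherent. With 100 patients per group, this would affect about 13 to 24 control and 9 to 17 YFXJD patients, assuming 90-day first and second supplies, perfect intake, exponential PFS with the protocol's medians, and a third supply ending between D270 and D365.

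The certain harm is an adherence rate that is biased low and a label tied to early stopping. The ITT comparison of PFS is untouched. Bias in the per-protocol analysis, and any difference between arms in mislabelling, each depend on a further condition that the document does not establish.

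**What to change.** Replace the formula with packets taken divided by packets due. Packets due are 2 per day, the protocol's own daily dose, from first dose to the earlier of permanent stop or the visit in question, less investigator-ordered interruptions or modifications. Keep the 80% threshold, and state whether the ratio is cumulative or per supply. If the per-protocol set is to use adherence, it should use this ratio.

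The text change is one sentence, and the dosing, dispensing schedule and threshold stay as they are. The cost is in data capture: treatment start and stop dates and the count of unused packets must be collected at the final visit. The article mentions return of empty packets and recording of interruptions, but not these items, so the case report form should be checked. With 38 of 200 patients enrolled at the July 2026 revision, this can still be settled well before analysis.

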##### Blinding assessment

A blinding success questionnaire will be administered at the end of treatment to assess whether participants and investigators could correctly guess treatment assignment.

##### Herb-drug interaction review

Osimertinib is primarily metabolized by hepatic CYP3A4. The following measures will be implemented: (1) systematic review of all herbal components for potential CYP3A4 interactions; (2) prohibition of concomitant herbal medicines known to interact with CYP3A4 (e.g., St. John’s Wort, Glycyrrhiza, Scutellaria); (3) specific monitoring for overlapping hepatic toxicity (ALT/AST every 4 weeks), gastrointestinal toxicity, and pulmonary toxicity (ILD monitoring); and (4) dose modification guidelines for osimertinib in case of grade ≥3 toxicity.

Participants who experience severe adverse events (AEs) assessed as related to the trial intervention will be provided with necessary post-trial medical care and may receive appropriate compensation in accordance with relevant regulations and the insurance protocol for this clinical trial. For any adverse reactions determined to be unrelated to the study medication, standard medical management will be provided based on a comprehensive assessment of the participant’s condition, including medical history, clinical symptoms, physical signs, and results from laboratory tests, imaging, and other diagnostic examinations.

#### Concomitant treatment regulations

During the trial, participants will be prohibited from using any anti-tumor or traditional Chinese medicine interventions that could affect the evaluation of efficacy or safety. Medications for coexisting chronic conditions that require ongoing treatment must be permitted but documented in the case report form (CRF).

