## Methods and analysis

### Study design

#### Trial design

This is a single-center, randomized, double-blind, placebo-controlled clinical trial with two parallel groups. A total of 200 patients with advanced EGFR-mutant NSCLC will be enrolled and randomly allocated in a 1:1 ratio to either the YFXJD group or the control group receiving placebo. Both groups will receive standard osimertinib therapy (80 mg orally once daily) throughout the study period.

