### Exclusion criteria

Participants will be excluded if they meet any of the following criteria:Known history of serious mental illness or cognitive impairment that, in the investigator‘s judgment, precludes the ability to provide informed consent or comply with the study procedures.History of active alcohol or drug abuse within the past year.Women who are pregnant, breastfeeding, or of childbearing potential who are unwilling to use a highly effective method of contraception during the study treatment period and for at least 3 months (or per specific EGFR-TKIs label requirement) there after.Uncontrolled or clinically significant cardiovascular disease, including but not limited to: symptomatic congestive heart failure (NYHA Class ≥II), unstable angina, myocardial infarction within the past 6 months, or uncontrolled arrhythmias.Poorly controlled hypertension (e.g., systolic blood pressure >150 mmHg or diastolic blood pressure >100 mmHg despite optimal medical management).Active, uncontrolled systemic infection requiring intravenous therapy.Any other severe, uncontrolled concomitant medical condition that, in the opinion of the investigator, would compromise the participant’s safety or interfere with the study evaluations.Receipt of any systemic anti-cancer therapy (including chemotherapy, immunotherapy, other targeted therapy, or investigational agents) within 4 weeks prior to the first dose of study treatment.Palliative radiotherapy to non-target lesions is permitted if completed >2 weeks prior to enrollment. Radiotherapy to target lesions or whole brain radiotherapy within 4 weeks prior to enrollment is excluded.Prior definitive chemoradiotherapy for stage III disease.Symptomatic, untreated, or unstable brain metastases or leptomeningeal disease requiring immediate local therapy (e.g., steroids, surgery, radiation). Participants with a history of treated brain metastases are eligible if they are radiologically stable (confirmed by MRI at least 4 weeks apart), asymptomatic, and do not require corticosteroid treatment for at least 2 weeks prior to the first dose.History of another primary malignancy.History of clinically significant interstitial lung disease (ILD), drug-induced ILD, or any evidence of active ILD on baseline imaging.Known severe hypersensitivity to any component of YFXJD or to osimertinib.Any condition that impairs oral drug absorption (e.g., inability to swallow, major gastrointestinal resection, active inflammatory bowel disease).

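### The concomitant-treatment rule admits every chronic-disease drug without exception, although CYP3A4 is named as osimertinib's main metabolic route and interacting agents are barred only when herbal

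*Protocol article*

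**What the plan says.** Three parts of the protocol article bear on this point.

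- **Concomitant treatment regulations.** The section has two rules. The first is a ban: participants are "prohibited from using any anti-tumor or traditional Chinese medicine interventions that could affect the evaluation of efficacy or safety". The second is a permission: "Medications for coexisting chronic conditions that require ongoing treatment must be permitted but documented in the case report form (CRF"). The permission has one condition, documentation, and no exception.
- **Herb-drug interaction review.** This section states that "Osimertinib is primarily metabolized by hepatic CYP3A4". Among its measures are a review of the herbal components for CYP3A4 interactions, the "prohibition of concomitant herbal medicines known to interact with CYP3A4" (the three examples given are all herbs), liver enzymes every 4 weeks with gastrointestinal and lung monitoring, and "dose modification guidelines for osimertinib in case of grade ≥3 toxicity".
- **Trial design.** On the dose: "Both groups will receive standard osimertinib therapy (80 mg orally once daily) throughout the study period".

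**The concern.** Whether an interaction through CYP3A4 matters depends on the agent's effect on that enzyme, not on whether the agent is a herb. The article treats the interaction as serious enough to ban a class of herbal products, and then obliges investigators to accept conventional long-term drugs with no corresponding check. A site that follows the printed text would start osimertinib 80 mg beside an interacting drug and do no more than write the drug down.

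What is at stake is limited. For the individual patient, osimertinib exposure could be altered without anyone having decided to accept that. For the data, the adverse-event outcome requires a judgement of each event's relationship to study treatment, and hepatic, gastrointestinal and pulmonary toxicity are monitored as overlapping. An interacting third drug makes that judgement harder case by case.

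**Working it through.** The article gives no figure on this point that could be reproduced, so the check is a reading of each printed rule that might remove a conventional CYP3A4-interacting chronic drug.

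1. **The ban in the same section.** The phrase about affecting the evaluation qualifies anti-tumor and traditional Chinese medicine interventions only. An ordinary drug for a chronic disease is neither. It falls under the second sentence, which permits it.

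2. **The CYP3A4 prohibition.** It is limited to herbal medicines, and so is the interaction review. That fits the section's title. The permission does not contradict it; the two rules simply do not meet.

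3. **Eligibility.** Inclusion criteria: 13. Exclusion criteria: 15. Total 13 + 15 = 28. The number that name CYP3A4 or interacting co-medication is 0. The catch-all exclusion concerns a severe, uncontrolled medical condition, not a drug. Patients on long-term treatment can enter: hypertension, for example, excludes only when poorly controlled (the diastolic limb reads "diastolic blood pressure >100 mmHg despite optimal medical management"). This shows that treated patients are eligible. It does not show that their drugs interact with CYP3A4.

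4. **Withdrawal/termination criteria.** The rule on prohibited concomitant therapy is confined to treatment directed at the lung cancer or its symptoms. The principal investigator may also end participation on health grounds, which is a general, case-by-case power and not a rule about co-medication.

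5. **Dose modification.** The only printed trigger for modifying the osimertinib dose is toxicity of grade 3 or higher. It acts after harm and not when the drug is co-prescribed. If an interaction lowered exposure instead of raising it, a toxicity trigger would not detect it. The secondary outcomes do count dose reductions and interruptions for any adverse event, whatever the grade, but that is an outcome to be recorded, not an instruction on when to act.

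6. **Timing of the medication record.** In Table 2 the concomitant-medication row is ticked at D0 (Baseline/Initiation), D90, D180 and D365, but not at screening. D0 is also the visit for randomization and dispensing. The section on randomization and blinding places randomization before the first osimertinib dose. So the information is scheduled to be collected at the visit where randomization precedes that dose; what is missing is a rule that acts on it. Some medication history is needed for eligibility anyway: patients with treated brain metastases must "do not require corticosteroid treatment for at least 2 weeks prior to the first dose".

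**How far a correction could reach.** Trial status reports 38 of 200 planned patients enrolled as of July 2026. Remaining: 200 − 38 = 162, and 162/200 = 81%. This measures how many patients could enter under a corrected rule. It is not an estimate of how many take an interacting drug; the documents give neither the frequency of such drugs nor the size of any exposure change.

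**The case against.** The strongest reply is that this is an omission presented as an error. Lists of prohibited drugs are commonly left to the full protocol, which is not shown, and a section on herb-drug interaction can be expected to speak only of herbs. On that view the chronic-medication sentence merely says that ordinary treatment lies outside the ban on cancer and Chinese-medicine therapies and has to be recorded. It permits treatment of the condition and does not stop an investigator from substituting an agent.

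Much of this stands. A reader might infer that the full protocol has no drug list, or that the two sections contradict each other; the article supports neither inference. The point that survives is narrower. The printed sentence is an obligation with no exception, so a list of barred chronic drugs held elsewhere would conflict with it, and the sentence would still need a qualifying clause.

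The existing safeguards also deserve weight: medications recorded at D0, liver enzymes every 4 weeks, monitoring for interstitial lung disease, and the principal investigator's power to end participation. They reduce the risk. None of them restricts an interacting drug in advance.

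It is also fair to say that clinical relevance is not shown. The article names the metabolic route but does not say that any particular conventional drug changes osimertinib exposure, in which direction, or how often such drugs are taken. Treated hypertensives illustrate who is eligible and no more.

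**Conclusion.** The point holds as a minor correction to participant safety and adverse-event attribution. The rule on chronic medications is fixed without the exception that the article's own statement about CYP3A4 calls for, and no other printed rule supplies it. The number of patients affected cannot be estimated from the documents.

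A reader might go further and infer a threat to the progression-free survival comparison. The documents do not support that. Allocation is randomized and double-blind, so use of interacting drugs should balance between arms, and nothing in the article allows any loss of power to be calculated. The trial's conclusion does not depend on this point.

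The conclusion rests on two assumptions: that sites would follow the sentence as printed, and that at least some conventional long-term drugs interact with osimertinib through CYP3A4 to a clinically relevant degree. The second is a matter for the clinical team to confirm.

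**What to change.** Amend the second sentence of the concomitant treatment regulations along these lines: *Medications for chronic conditions are allowed and recorded, except those with a clinically relevant CYP3A4 interaction with osimertinib; these are to be substituted, or otherwise managed by the clinical team, before the first osimertinib dose.* The clinical team decides which agents this covers and how each is handled.

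Use the existing concomitant-medication record at D0 for the check. If convenient, also tick that row of Table 2 at screening. Screening is at D −7, so this would allow about a week to review or change a drug before randomization. No new case report form item is needed.

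Cost: one clause, at most one extra tick in Table 2, and an amendment approved by the ethics committee. It would apply to the 162 patients not yet enrolled at the July 2026 status, together with a review of the medications already recorded for the 38 enrolled. The downside is that a few candidates will need a medication review or a change to a stable chronic drug. Such a change carries some risk of its own, which is why the clause leaves room for management other than substitution.
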